**Basis of Dosage Design**

The initial and maximum doses for this trial were determined based on both data from preclinical animal trials and data from clinical trials of TDM-1 and SGN-35 on the market, combined with the Phase I clinical trial conducted simultaneously.

The following refers to the relevant experimental data of the listed TDM-1 and SGN-35. Refer to Table 2 for details.

**Table 2. Comparison of general information on 3 types of ADC drugs.**

| **ADC Study Code** | **RC48-ADC** | **TDM-1** | **SGN-35** |
| --- | --- | --- | --- |
| **Common Name** | Recombinant Humanized Anti-HER2 Monoclonal Antibody-MMAE Conjugate for Injection | Ado-trastuzumab emtansine | Brentuximab vedotin |
| **Brand Name** | None | KADCYLA | ADCETRIS |
| **Antibody** | HER2 | HER2 | CD30 |
| **Molecule** | MMAE | DM1 | MMAE |
| **Antibody Target** | HER2 | HER2 | CD30 |
| **Tumor-bearing Mice**  **Effective Dose** | 1.5 mg/kg | 5 mg/kg | 1 mg/kg |

MTDs of RC48-ADC (Q2W x 7), SGN-35 (Q3W x 4) and TDM-1 (Q2W x 4) were 10, 3 and 10 mg/kg respectively. MTDs of RC48-ADC and TDM-1 were similar, while SMD-35 had the lowest MTD.

Effective doses of RC48-ADC and TDM-1 in Herceptin-resistant animal models were 1.5 mg/kg and 5 mg/kg respectively, and those in herceptin- and lapatinib-resistant animal models were 5 mg/kg and 15 mg/kg respectively. Hence, the estimated effective dose of RC48-ADC is approximately one-third of TDM-1. The effective dose of SGN-35 in animal in vivo efficacy study was 1 mg/kg, slightly lower than that of RC48-ADC, hence the effective doses of these two drugs are equivalent. Among these three ADC drugs, SGN-35 has the lowest effective dose and MTD, while TDM-1 has the highest effective dose and MTD. The effective dose of RC48-ADC is similar to that of SGN-35, and its safe dose is similar to TDM-1. Therefore, the therapeutic window of RC48-ADC is the largest among the three drugs. The recommended dose of listed SGN-35 is 1.8 mg/kg. Based on the comparison of animal experimental data, the effective dose of RC48-ADC is similar to that of SGN-35, hence the effective dose of RC48-ADC is expected to be greater than 1.8 mg/kg.

The molecular weight of RC48-ADC is 149 kD. Therefore, RC48-ADC is considered to be an intravascularly administered protein with a molecular weight of more than 100 kD and should be measured in mg/kg.

According to the "Guiding Principles for Clinical Trial Techniques of Anti-Tumor Drugs" and "Technical Guidelines for Non-Clinical Studies of Cytotoxic Anti-Cancer Drugs" issued by China, the initial dose of Phase I clinical trials was estimated as follows: the MTD obtained from rat multiple-dose toxicological study was 12 mg/kg, with the equivalent dose for human was 1.92 mg/kg and the safety factor was 10. The calculation of 1/10 gave the initial dose of 0.192 mg/kg. As a related animal, crab-eating macaque was given multiple doses (Q2W x 7) during toxicological study, providing an MTD of 10 mg/kg. The human equivalent dose was 3.2 mg/kg and the calculation of 1/6 gave the initial dose of 0.53 mg/kg.

According to the FDA's "Estimating the Maximum Safe Starting Dose in Initial Clinical Trials for Therapeutics in Adult Healthy Volunteers", the starting dose was calculated to be 0.096 mg/kg, which was approximately equal to 0.1 mg/kg.

**Table 3. Comparison of calculation results from different animal data.**

| species | NOAEL | kmanimal/kmhuman | HED | MRSD |
| --- | --- | --- | --- | --- |
| Rat | 6 mg/kg | ×0.16 | 0.96 mg/kg | 0.096 mg/kg |
| Crab-eating Macaque | 3 mg/kg | ×0.32 | 0.96 mg/kg | 0.096 mg/kg |

Based on the above data, investigators decided to select 0.1 mg/kg as the initial dose and 1 patient to collect a single set of pharmacokinetics. In order to reduce the patient's exposure to an ineffective dosage, the patient do not undergo further administration of this dosage. The 2nd dose is 0.5 mg/kg and 1 patient is selected for the collection of a single set of pharmacokinetics. There is an interval of 21 days after the first administration. Based on the results of the single sets of pharmacokinetics from these 2 patients within 21 days, investigators should decide whether the interval of administration in this trial is Q1W, Q2W or Q3W. Q2W was tentatively selected at a meeting on Jan. 26, 2016. Each treatment cycle includes 2 doses.

Repeated doses are given to subjects from the second dose (0.5 mg/kg) forward to collect pharmacokinetic data of repeated doses. Pharmacokinetic data are collected before and after each of 4 doses for one patient, no matter what dosing interval is used.

# 6. Blood Collection Times and Outcome Measures

According to the results of non-clinical pharmacokinetics and clinical trial literature of TDM-1[4-6], the following times are tentatively set for blood collection. The first dose group uses the following blood collection points. Specific times of collection may be adjusted, added or subtracted based on the characteristics of RC48-ADC during the actual trial. The tentative blood collection times are as follows.

**Blood Collection for PK During Dose-Escalation Trial:**

Blood collection time points for Q2W administration:

The blood collection points for the first dose (11 blood collection points): before administration (0 h), 0.25 h, at the end of infusion, 1.5 h, 12 h, 24 h, 48 h, 72 h, 120 h, 168 h and 240 h.

For the second dose (1 blood collection point): before administration (336 h).

For the third dose (1 blood collection point): before administration (672 h).

For the fourth dose (12 blood collection points): before administration (1008 h), 0.25 h (1008.25 h), at the end of infusion, 1.5 h (1009.5 h), 12 h (1020 h), 24 h (1032 h), 48 h (1056 h), 72 h (1080 h), 120 h (1128 h), 168 h (1176 h), 240 h (1248 h) and 336 h (1344 h).

Blood samples are collected at these 25 time points to detect serum ADC, TAb and free MMAE, with a collection volume of 2 mL each time.

Blood collection points for immunogenicity (ADA) assays: Serum anti-ADC antibodies are detected before the first, second, third and fourth doses, and 336 hours after the fourth dose (5 collection points), with 1 mL of blood volume for each sample.

Blood collection time points for Q3W administration:

The blood collection points for the first dose (11 blood collection points): before administration (0 h), 0.25 h, at the end of infusion, 1.5 h, 12 h, 24 h, 48 h, 72 h, 120 h, 168 h and 240 h.

For the second dose (1 blood collection point): before administration (504 h).

For the third dose (12 blood collection points): before administration (1008 h), 0.25 h (1008.25 h), at the end of infusion, 1.5 h (1009.5 h), 12 h (1020 h), 24 h (1032 h), 48 h (1056 h), 72 h (1080 h), 120 h (1128 h), 168 h (1176 h), 336 h (1344 h) and 504 h (1512 h).

Blood samples are collected at these 24 time points to detect serum ADC, TAb and free MMAE, with a collection volume of 2 mL each time.

Blood collection points for immunogenicity (ADA) assays: Serum anti-ADC antibodies were detected before the first, second and third doses, and 504 h after the third dose (4 collection points), with 1 mL of blood volume for each sample.

Blood collection time points for QW administration:

The blood collection points for the first dose (9 blood collection points): before administration (0 h), 0.25 h, at the end of infusion, 1.5 h, 12 h, 24 h, 48 h, 72 h and 120 h.

For the second dose (1 blood collection point): before administration (168 h).

For the third dose (1 blood collection point): before administration (336 h).

For the fourth dose (10 blood collection points): before administration (504 h), 0.25 h (504.25 h), at the end of infusion, 1.5 h (505.5 h), 12 h (516 h), 24 h (528 h), 48 h (552 h), 72 h (576 h), 120 h (624 h) and 168 h (672 h).

Blood collection points for immunogenicity (ADA) assays: Serum anti-ADC antibodies are detected before the first, second, third and fourth doses, and 336 hours after the fourth dose (5 collection points), with 1 mL of blood volume for each sample.

**Blood Collection for PK During Extended Trial:**

Blood collection time points for Q2W administration:

The blood collection points for the first dose (11 blood collection points): before administration (0 h), 0.25 h, at the end of infusion, 1.5 h, 12 h, 24 h, 48 h, 72 h, 120 h, 168 h and 240 h.

For the second dose (1 blood collection point): before administration (336 h).

For the third dose (1 blood collection point): before administration (672 h).

For the fourth dose (12 blood collection points): before administration (1008 h), 0.25 h (1008.25 h), at the end of infusion, 1.5 h (1009.5 h), 12 h (1020 h), 24 h (1032 h), 48 h (1056 h), 72 h (1080 h), 120 h (1128 h), 168 h (1176 h), 240 h (1248 h) and 336 h (1344 h).

Blood samples are collected at these 25 time points to detect serum ADC, TAb and free MMAE, with a collection volume of 2 mL each time.

Blood collection points for immunogenicity (ADA) assays: Serum anti-ADC antibodies are detected before the first, second, third and fourth doses, with 1 mL of blood volume for each sample.

After the first efficacy evaluation, 3 mL of blood is collected before each administration to detect serum ADC, TAb, free MMAE and serum anti-ADC antibodies.

**Method of Blood Collection**: Please refer to RC48-ADC Blood Sampling Procedure for specific details.

**Unexpected Blood Collection for PK:** A blood sample of 2 mL is taken for PK analysis immediately no later than 72 hours after SAEs, DLT or dosing suspension.

The above blood samples will also be used for exploratory purposes.

In consideration of rationality and operability, deviations in PK blood collection time points are permitted, as detailed below:

Prior to medication through 6 h postdose: Scheduled time point±3 min.

6 h postdose through 24 h postdose: Scheduled time point±10 min.

24 h postdose through 21 days postdose: Scheduled time point±30 min.

On July 4, 2017, blood collection time frame was adjusted in consideration of accuracy of PK analysis and clinical practice, as detailed below:

Prior to medication: In 30 min.

0.25 h after medication starts through end of drip: ±3 min.

1.5 h after medication starts: ±5 min.

12 h after medication starts: ±30 min.

24 h after medication starts: 1 h Prior to the next dose: ±2 h.

# 7. Outcome Measures

(1) Demographic data: Age, sex, height, and body weight.

(2) Vital signs: Respiration, sitting blood pressure, sitting pulse, and body temperature.

(3) Physical examination: Nervous system, mental system, respiratory system, cardiovascular system, gastroenteric system, and skin. ECOG evaluation;

(4) Laboratory test

Table 4 lists items of laboratory test to be performed during the study. For specific test time points, please see Appendix 2 Trial Flow Chart.

**Table 4. Laboratory test items.**

| **Item Name** | **Examination Including** |
| --- | --- |
| Virology test | 5 liver function tests, HCV, and HIV |
| Routine blood test | RBC, Hb, WBC, NEUT, EO, BA, LY, and PLT |
| Blood chemistry | Myocardial zymogram (CK-MB), cTn, GGT, ALT, AST, ALP, TP, ALB,  ALB/GLO, TBIL, IBIL, ^DBIL,^ BUN, Cr, Glu, K+, Na^+^, Cl^－^, LDH, TC, TG, HDL-C, and LDL-C |
| Blood coagulation test | International Normalized Ratio (INR), prothrombin time (PT), and Activated partial thromboplastin time (APTT) |
| Routine urinalysis + urine pregnancy test | SG, pH, U-PRO, U-GLU, U-RBC, U-WBC, and HCG pregnancy test (for females during child-bearing period) |
| PK★ | Total antibody in serum, ADC and free MMAE Plasma concentration |
| Immunogenicity★ | Serum anti-ADC antibody (ADA, anti-RC48-ADC antibody) |
| Tumor markers | Specific test items will be determined by the investigators depending on the tumor type |

★ Blood samples for PK and immunogenicity assays shall be handled as per blood sample handling procedure, and then sent by the sponsor to a designated laboratory for assay.

(5) Imaging Examination

At baseline, all patients with solid tumors must undergo CT/MRI scans of the chest, abdomen and pelvis according to the RECIST v1.1. For osteopathy patients, confirmatory bone scan shall be carried out at the time of baseline. Tumor assessment will be performed by using CT/MRI/radiography.

(6) ECG: ECG (12-lead) examination will be conducted 3 times with an interval of 5 min prior to each dose.

ECG monitoring will be carried out during medication.

ECG (12-lead) examination will be conducted 3 times with an interval of 5 min within 1-2 h postdose.

(7) Efficacy Evaluation

Objective Response Rate (ORR) refers to a percentage of patients whose tumors have shrunk to a given volume and maintained for a period, it includes PR+CR (as per RECIST 1.1).

At the dose-escalation trial phase, efficacy in each patient will be evaluated after every 2 treatment cycles, wherein one treatment cycle consists of 2 doses. For patients dosed Q3W, efficacy evaluation will be conducted after every 3 treatment cycles, wherein one treatment cycle consists of 1 dose.

At the extended trial phase, efficacy evaluation will be carried out for each subject according to the following evaluation criteria every 2 treatment cycles. ORR will be calculated on the basis of result of this evaluation.

For subjects rated as CR or PR at the initial evaluation, their efficacy should be verified 4 weeks later.

Improvement or worsening of general conditions will be expressed by variation in ECOG score before and after treatment.

**Evaluation Criteria**

In accordance with RECIST 1.1, objective evaluation criteria for antineoplastic drugs are established as follows:

**Complete Response (CR)** All target lesions disappear, and minor diameter of any pathological lymph node (including target and non-target nodes) shall be decrease by < 10 mm.

**Partial Response (PR)** Sum of diameters of target lesions is less than baseline level at least by 30%.

**Stable Disease (SD)** Target lesions neither shrink to a level of PR nor enlarge to a level of PD, and the minimum of sum of their diameters can serve as a reference value for the study.

**Progressive Disease (PD)** With the minimum of sum of diameters of all measured target lesions throughout the study as a reference, relative increase in sum of diameters is at least 20% (a baseline measurement will serve as the reference if it is the smallest value); in addition, absolute value of sum of diameters has to increase by at least 5 mm (occurrence of one or more new lesions is deemed PD, too).

(8) Safety and Tolerance Assessment

Body weight of each patient is to be measured prior to each treatment, which will be used in PK calculation.

When being subjected to blood pressure and pulse measurement, a subject must rest in sitting position for at least 3 min. Each measurement of blood pressure shall be taken on the same arm.

Result of 12-lead ECG will be recorded during the trial. The records include ECG date and time, heart rate, PR interval, QT interval, QTcB duration, and QRS duration. In overall evaluation, whether or not any clinically significant abnormality is found shall be defined. Clinically significant abnormalities, if any, have to be further defined. Signed original ECGs will be archived in the study site.

If laboratory test results of a patient during the screening period are out of a range specified in the protocol, then they can be reviewed once prior to enrollment. If the review result is still out of specification range, then this patient cannot be included in the trial.

If the result of a laboratory test of a patient during the screening period is out of normal range but this test is not specified in the protocol, then it will be judged by the investigators whether it is clinically significant or not. This test may be repeated once as soon as possible in a bid to eliminate laboratory error.

If there occurs a QTcF interval > 500 ms or increasing by > 60 ms relative of the baseline or grade III atrioventricular block during trial, then the trial medication should be suspended. The investigators will decide whether or not to continue medication after defining its cause.

In a non-DLT observation cycle, if any clinically significant AE occurring in one subject is judged by the investigators to be potentially, probably or definitely relevant to the study drug, and this AE is likely to continue or be potentially aggravated in the next scheduled dosing, then the investigators may postpone dosing or stop one dose of the study drug, the delay may last for up to 21 days or dose level may be lowered by 1 or 2.

The following provisions apply to toxic reaction occurring beyond DLT evaluation window.

Non-Hematological Toxicity

If any grade 4 non-hematological toxicity occurs in a patient postdose, or there occurs any important injury of organs such as lungs, cardiovascular system, liver and kidneys, then treatment of the patient should be immediately terminated.

If a patient gets any clinical benefit after treatment, but exhibits over grade 3 non-hematological toxicity (except hair loss, nausea, and emesis) and can be recovered to normal, grade 1 or baseline level in 14 days after the optimal supportive therapy, then one dose reduction is allowed. The specific dose shall be determined by the investigators and the sponsor through mutual negotiation (it may be a previous dose subjected to safety assessment or an arbitrary dose previously assessed). If the subject fails to be recovered to normal, grade 1 or baseline level in 14 days, then the investigators and the sponsor will discuss and decide whether or not to terminate the study treatment. If a toxic reaction occurs at the first dose level, then the dose can be reduced to 50%. Subsequent dose escalation trial will be adjusted by the investigators and the sponsor through negotiation.

Hematological Toxicity

If a patient gets any clinical benefits after treatment but exhibits grade 4 neutropenia, neutropenic fever, thrombocytopenia, anemia or grade 3 thrombocytopenia with bleeding tendency, then trial medication should be suspended until the toxic reactions are recovered to normal level or Grade 1. If toxicity is recovered to normal or grade 1 level in 14 days, then one dose reduction is allowed to continue treatment; if toxicity fails to be recovered to normal or grade 1 level in 14 days, then the investigators and the sponsor will discuss and decide whether or not to continue the treatment, one dose reduction will be conducted if continued patient treatment is allowed.

Toxicity Relapse

If a patient exhibits again the same grade 3 or above non-hematological toxicity or grade 4 hematological toxicity after a dose reduction, then treatment of the patient shall be stopped.

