## 8.3 Extended Trial

Patients evaluated as CR, PR and SD in the first efficacy evaluation during dose escalation phase can enter the extended trial on a voluntary basis, provided that investigators estimate that continuous medication would be beneficial to the patient. A time frame of ±3 days is allowed for all tests (except imaging examination) for each visit. An extended trial should include the following tests:

- ECOG evaluation;
- Body weight measurement, physical examination and vital sign examination for 1 time;
- Examine the following items before each administration: routine blood test, routine urinalysis, blood chemistry (Troponin, GGT, ALT, AST, ALP, TP, ALB, ALB/GLO, TBIL, IBIL,DBIL, BUN, Cr, Glu, K+, Na+, Cl－, LDH, TC, TG, HDL-C, and LDL-C);

On July 4, 2017, the investigators and sponsor decided to discontinue the original dose-escalation study starting with 2.0 mg/kg Q3W. Instead, a dose-escalation study with an initial dose of 1.25 mg/kg QW was added. Subjects participating in the extended trial should undergo routine blood test, routine urinalysis, blood biochemical examination before the initial administration of each treatment cycle;

- Tumor markers (specific test items will be determined by the investigators depending on the tumor type);
- ECG examination before each administration; if the subject experiences precordial chest pain, palpitations or other symptoms, or has an abnormal ECG, CK-MB test and echocardiography may be added;

On July 4, 2017, the investigators and sponsor decided to discontinue the original dose-escalation study starting with 2.0 mg/kg Q3W. Instead, a dose-escalation study with an initial dose of 1.25 mg/kg QW was added. Subjects participating in the extended trial should undergo ECG examination before the initial administration of each treatment cycle. If the subject experiences precordial chest pain, palpitations or other symptoms, or has an abnormal ECG, CK-MB test and echocardiography may be added;

- Tumor imaging examination, including CT or MRI scans of the chest, abdomen, pelvis, brain and other related lesions. For subjects rated as CR or PR at the initial evaluation, their efficacy should be verified 4 weeks later. A time frame of ±7 days is allowed. Specific evaluation time points are as follows:
  - once every 2 treatment cycles;
  - when the treatment ends or subject withdraws.

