## 10.2 Drugs may be Conditionally Used During Study

When non-DLT adverse events occur during the DLT observation period of the dose escalation phase, no medical treatment (including but not limited to dosing suspension and symptomatic treatment) should be provided in principle in order to observe possible adverse reactions (including severity and reversibility) to the investigational drug. Once any DLT toxic reactions specified in the protocol occur, medication must be discontinued immediately and active treatment must be provided. Medications should be recorded on CRF. Adverse events occurring during the non-DLT observation period should be dealt according to "(8) Safety and Tolerability Evaluation" of outcome measures described in Protocol 7.

On July 4, 2017, the investigators and sponsor determined that during the dose escalation phase starting with 2.5 mg/kg Q2W and dose-escalation trial with an initial dose of 1.25 mg/kg QW, adverse events occurred within the DLT observation period may be dealt with symptomatic treatments as necessary upon investigators' judgment; G-CSF treatment is allowed for Grade 4 neutropenia but prohibited for preventive application. Once any DLT toxic reactions specified in the protocol occur, medication must be discontinued immediately and active treatment must be provided. Medications should be recorded on CRF.

In principle, medication should not be discontinued when a subject experiences a toxic reaction during the extended trial. Doctors may administer appropriate treatment according to the specific situation based on the following principles:

Doses are escalated in an order of 2 mg/kg, 1.5 mg/kg, 1 mg/kg and 0.5 mg/kg, with 0.5 mg/kg as the lowest dose.

Myelosuppression: In case of myelosuppression, investigators may perform symptomatic treatments based on clinical manifestations. If Grade III or higher neutropenia occurs, GSF treatment should be provided. Specific dose modification is shown in Table 5.

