**Table 5. Dose modification criteria for myelosuppression.**

| **Myelosuppression** | **Treatment Adjustment** | **Dose Modification for Next Course of Treatment** |
| --- | --- | --- |
| Grade I and II | Maintain original dose | Maintain original dose |
| Grade III neutropenia/Grade III thrombocytopenia | | |
| First occurrence | Delay medication until recovered to ≤ Grade I | Maintain original dose |
| Second occurrence | Delay medication until recovered to ≤ Grade I | Decrease by 1 dose level |
| Grade IV neutropenia/Grade III neutropenia with fever/Grade IV thrombocytopenia | | |
| First occurrence | Delay medication until recovered to ≤ Grade I | Decrease by 1 dose level |
| Second occurrence | Discontinue medication |  |

Impaired liver function: When the patient experiences liver function damage, treatment of liver protection may be administered and preventative measures can be provided in subsequent treatments. Specific dose modification is shown in Table 6.

Neurotoxicity: When patients develop neurotoxicity, preventative medication may be administered in subsequent treatments. Specific dose modification is shown in Table 6.

Diarrhea: When the patient experiences loose stools or diarrhea, antidiarrheal medication is recommended. Specific dose modification is shown in Table 6.

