**Table 6. Dose modification criteria for impaired liver function, neurotoxicity and diarrhea.**

| **ALT and AST abnormalities**  **\Neurotoxicity\Diarrhea** | **Treatment Adjustment** | **Dose Modification for Next Course of Treatment** |
| --- | --- | --- |
| Grade I and II | Maintain original dose | Maintain original dose |
| ≥ Grade III | | |
| First occurrence | Delay medication until recovered to ≤ Grade I | Maintain original dose |
| Second occurrence | Delay medication until recovered to ≤ Grade I | Decrease by 1 dose level |
| Third occurrence | Discontinue medication |  |

Rashes: Symptomatic treatments may be applied when rashes occur. Specific dose modification is shown in Table 7.

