# 18. Content Added During the Trial

On Oct. 18, 2016, the investigators and sponsor decided to add a dose-escalation trial with Q3W administration in the dose-escalation phase. Starting from the 2.0 mg/kg dose group, 2-3 patients are enrolled. Pharmacokinetic data from Q3W administration are collected repeatedly. The dose next to 2.0 mg/kg is determined based on the results of the dose escalation study with Q2W administration. The extended trial is started with the 2.0 mg/kg dose group. Pharmacokinetic data from Q2W administration are collected repeatedly. The dose next to 2.0 mg/kg is determined by the investigators. Q2W dosing means 1 treatment cycle includes 2 doses. The efficacy evaluation is performed once every 2 treatment cycles.

On July 4, 2017, the investigators and sponsor decided that:

(1) Symptomatic supportive treatment is allowed in the DLT evaluation period. Dose escalation trials are performed according to the traditional 3+3 mode, wherein doses are proposed to be escalated from 2.5 mg/kg to 3.0 mg/kg, 3.5 mg/kg and 4.0 mg/kg with Q2W administration until MTD is reached, or the sponsor and investigators decide to terminate the escalation study.

(2) The original dose-escalation study starting with 2.0 mg/kg Q3W was discontinued. Instead, dose escalation trial is carried out with an initial dose of 1.25 mg/kg, followed by 1.5 mg/kg, in the traditional 3+3 mode with QW administration. Symptomatic supportive treatment is allowed in the DLT evaluation period until MTD is reached. If the 1.5 mg/kg dose group does not reach MTD, the sponsor and investigators will jointly decide on the next escalating doses or whether to terminate the dose escalation trial. The DLT for this phase is defined as follows:

DLT refers to the following toxic reactions observed in the DLT evaluation window (observation period of Day 1-21 after the first dose) that are considered related to RC48-ADC treatment by the investigators or sponsor, wherein the grading is based on the 5-level system of the CTCAE v4.0:

- Grade 4 neutropenia lasting more than 3 days after symptomatic treatment; or grade 4 neutropenia recurring after recovery to a normal level through symptomatic treatment.
- Neutropenic fever (defined as absolute neutrophil count [ANC] < 1000/mm3 accompanied by a fever higher than 38.3 °C or a fever above 38 °C that persists for more than 1 h).
- Grade 3 neutropenia with confirmed infections.
- Grade 3 thrombocytopenia with bleeding tendency.

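### Table 6 returns a first Grade IV liver-enzyme, neurotoxicity or diarrhea event to the original dose after recovery, where Section 7(8) terminates treatment; Section 11.3 also cuts the dose for neuropathy where Table 6 does not

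*Protocol*

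**What the plan says.** Section 7, item (8) sets general rules after the DLT period. Their scope is "The following provisions apply to toxic reaction occurring beyond DLT evaluation window", with no limit to one phase. The first non-hematological rule opens "If any grade 4 non-hematological toxicity occurs in a patient postdose" and ends in immediate termination of that patient's treatment.

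Section 10.2 sends events outside the DLT observation period to Section 7(8), in a paragraph about dose escalation. A later paragraph turns to the extended trial: "In principle, medication should not be discontinued when a subject experiences a toxic reaction during the extended trial". It then gives a dose ladder, "Doses are escalated in an order of 2 mg/kg, 1.5 mg/kg, 1 mg/kg and 0.5 mg/kg, with 0.5 mg/kg as the lowest dose", and Tables 5 to 8. Table 6 covers ALT/AST abnormalities, neurotoxicity and diarrhea in two bands: Grade I-II, where the dose is kept, and Grade III or higher. For the upper band it says "First occurrence | Delay medication until recovered to ≤ Grade I | Maintain original dose". There is no Grade IV row.

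Section 8.3 brings escalation patients into the extended trial: "Patients evaluated as CR, PR and SD in the first efficacy evaluation during dose escalation phase can enter the extended trial".

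Section 11.3 says that patients with new or worse peripheral sensory neuropathy had their dose lowered by 1-2 levels, and were stopped if it did not resolve. It gives no grade threshold.

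**The concern.** For the same first Grade IV event, a site that opens Section 7(8) ends treatment, while a site that opens Table 6 waits for recovery and gives the full dose again. Safety is a primary objective (Section 2), and these rules decide who is re-exposed and at what dose.

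The neuropathy mismatch concerns an event already seen in this trial. Section 1.5 names numbness of hands and feet among the events that led to changes in medication. The protocol elsewhere treats Grade 2 neurotoxicity as material: Grade 2 or higher neuropathy excludes at entry (Section 4.2, item 15), and Grade 2 or higher neurotoxicity persisting to the next dose is a DLT (Section 3). Table 6 keeps the dose unchanged at that grade.

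**Working it through.** The plan gives no figure to reproduce. The check is to establish which patients fall under both rule sets, compare the actions, and size the cost of the fix.

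**1. Overlap in time.** The DLT window is Day 1-21 after the first dose. The first efficacy evaluation follows the fourth dose. From the sampling times in Section 6, the fourth dose falls at 1008/24 = 42 days after the first dose (Q2W) or 504/24 = 21 days, that is Day 22 (QW). Every Q2W or QW rollover patient is therefore past the window and within the stated scope of Section 7(8), and is also in the extended trial, where Tables 5-8 apply.

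**2. Actions compared at 2.0 mg/kg.** The ladder is 2.0, 1.5, 1.0, 0.5 mg/kg. One level down is (2.0 − 1.5)/2.0 = 25%; two levels down is (2.0 − 1.0)/2.0 = 50%.

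| Event | Table 6 | Other rule |
| --- | --- | --- |
| First Grade IV ALT/AST, neurotoxicity or diarrhea | Hold to Grade I or lower, then 2.0 mg/kg (0% cut) | Section 7(8): terminate |
| New or worse sensory neuropathy, Grade I-II | 2.0 mg/kg (0% cut) | Section 11.3: 1.5 or 1.0 mg/kg (25% or 50% cut) |
| First sensory neuropathy of Grade III or higher | Hold to Grade I or lower, then 2.0 mg/kg (0% cut) | Section 11.3: 1.5 or 1.0 mg/kg (25% or 50% cut) |

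**3. Dose levels for rollover patients.** Section 18 continues escalation: "wherein doses are proposed to be escalated from 2.5 mg/kg to 3.0 mg/kg, 3.5 mg/kg and 4.0 mg/kg with Q2W administration". These doses lie above the Section 10.2 ladder, but Table 1 in Section 5 lists Q2W levels in 0.5 mg/kg steps from 0.5 to 4.0 mg/kg, so the level below each is known. Of the QW doses (1.25 and 1.5 mg/kg), only 1.25 mg/kg is on neither list.

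**4. Cost of a Grade IV stop.** Section 1.5 gives no grades for non-hematological events, so the rate p of a first Grade IV Table 6 event per subject is assumed. The directly enrolled extension has at least 10 + 20 = 30 subjects. Expected number = 30p; chance of at least one = 1 − (1 − p)^30.

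| Assumed p | 30p | 1 − (1 − p)^30 |
| --- | --- | --- |
| 1% | 0.3 | 26% |
| 3% | 0.9 | 60% |
| 5% | 1.5 | 79% |

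These figures size what the stop would cost directly enrolled subjects. They do not measure how often rollover patients would meet the conflict.

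**The case against.** The strongest reply is that Section 10.2 already splits the rules by phase. Its escalation paragraph points to Section 7(8), its extended-trial paragraph introduces Tables 5-8, and rollover patients are said to enter the extended trial. Section 7(8) also reads in places as escalation text. This is the better reading for rollovers and direct enrollees alike. It remains an inference: Section 7(8) states its scope without a phase, and no sentence gives precedence. Nor does accepting it remove the full-dose re-treatment; it confirms it.

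A second reply is that safeguards exist. Table 6 requires recovery to Grade I or lower, and delays outside the DLT period are capped at 21 days (Sections 7(8) and 9). Section 11.1 stops the drug at a serious adverse event, a category that includes temporary organ damage, and Section 4.3 withdraws patients made unsuitable by a severe event. A reader might infer that the protocol re-doses automatically with nothing in the way; it does not. But Section 11.1 defines seriousness by outcome rather than CTCAE grade and does not call the stop permanent, and Section 4.3 rests on judgment. The risk is reduced and the conflict stays.

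A third reply is that the Section 11.3 sentence is past-tense narrative placed after literature on another drug. That is fair as to form. It directly follows this trial's own exclusion criterion and states a dose action, so a site could apply it.

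Two stronger readings are not supported. One is that differing grade bands are themselves an error, since Table 5 gives severe events their own row ("Grade IV neutropenia/Grade III neutropenia with fever/Grade IV thrombocytopenia") and Table 8 has a Grade IV row. The tables cover different toxicities, and the sponsor may band them differently. The other is that dose reductions are undefined for most rollover doses. Table 1 supplies the Q2W levels, and the gap is 1.25 mg/kg QW alone.

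**Conclusion.** The point holds and should be fixed. Table 6 as written permits full-dose re-treatment after a first Grade IV event, once recovered, of a kind that Section 7(8) treats as terminating. The neuropathy action in Section 11.3 also differs from Table 6. At 2.0 mg/kg the contrasts are termination against a 0% cut, and a 25-50% cut against none.

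This follows from the text alone. The only assumption is the 1-5% Grade IV rate, used to size the cost of the fix. A reader might infer that the MTD is at risk; it is not, because Section 7(8) acts after the DLT window and Table 6 in the extended trial, so DLT counts are unaffected.

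**What to change.** (a) Add a Grade IV row to Table 6 set to discontinue, consistent with Section 7(8) and with Table 8. This is the substantive change: a precedence sentence alone would settle the conflict in favor of full-dose re-treatment.

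(b) State in Sections 7(8) and 10.2 that Tables 5-8 govern all extended-trial patients, including those who roll over under Section 8.3. Use the Table 1 levels for Q2W doses above 2.0 mg/kg, and name the step below 1.25 mg/kg QW.

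(c) Replace the neuropathy sentence in Section 11.3 with a reference to Table 6, or amend Table 6 to match it.

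Optional clarifications are a Grade IV row for rash in Table 7 and a statement of whether the serious-event stop in Section 11.1 is permanent.

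The cost is amendment wording and one table row, with no added visits, samples or subjects. The downside is that a few patients who recover from a Grade IV event lose further treatment: 0.3 to 1.5 of the 30 directly enrolled subjects at the assumed rates.
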